### Power and Sample Size Analysis

A post hoc analysis using the results of the MANOVA test for the reported sample population on our preliminary data was conducted using G*Power version 3.1.9.2. Statistical power was computed using a sample of n=30 and the identified 3 DVs at resting baseline condition. Alpha level was set at alpha=<.05. The results of our post hoc analyses suggest that our effect size (*f*^2^=0.120) is considerably in the medium range [93], whereas power was low at 0.283. This is considerably different from the initial set sample size of n=32 (alpha=.05, *d*=0.80, *P*=.80). With this in mind, we then recomputed the required sample size using a priori methods, setting a moderately large effect size of *f*^2^=0.625 and a power of 0.80 for the needed 4 groups among 3 response variables to be used as DVs. Our post hoc analysis suggests that the current samples (n=15 per group) included in our pilot findings are underpowered; hence, significant effects may not yet be seen. On the basis of our results, the needed sample for this research is computed at n=22 per group (Table 2).

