**Methods:**

In this study, we intend to recruit 128 children from different ethnic groups or environment contexts as follows: (1) 32 typically developing Chinese children living in Hong Kong; (2) 32 typically developing Filipino children living in Hong Kong; (3) 32 typically developing Filipino children who are living in urban areas; and (4) 32 typically developing Filipino children who are living in rural areas in Philippines. Autonomic activity (heart rate variability [HRV] and electrodermal activity [EDA]) will be measured and recorded using Polar H2 heart rate monitor and eSense GSR skin response sensor. Autonomic activity (HRV-low frequency, HRV-high frequency, and EDA) at different conditions between pairwise groupings will be tested using multivariate analysis of variance (MANOVA). All significant levels will be set at *P* ≤.05.

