**Input**		
	Effect size *f*^2^(*V*)	0.0625
	α err prob^b^	0.0500
	Power (1- *β* err prob)^c^	0.8000
	Number of groups	4
	Response variables	3

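### The text gives the planning effect size as f²=0.625, but Table 2's N=88 rests on 0.0625, and no passage says whether 128 or 88 children is the final target

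*Protocol article*

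**What the plan says.** The Results subsection Power and Sample Size Analysis first reports a post hoc calculation on the pilot: f²=0.120, described as medium, with power 0.283. It then describes a new a priori calculation, "setting a moderately large effect size of *f*^2^=0.625 and a power of 0.80", for four groups and three response variables. It concludes that "the needed sample for this research is computed at n=22 per group" and refers to Table 2.

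The input block of Table 2 reads "Effect size *f*^2^(*V*) 0.0625", with "Number of groups 4", "Response variables 3", alpha 0.05 and power 0.80. Its footnote names the test as the MANOVA global-effects F test. Its outputs are λ=16.5, critical F=1.9171, df 9 and 252, total sample size 88, actual power 0.8094 and Pillai V=0.1765.

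The Methods paragraph of the Abstract says "we intend to recruit 128 children from different ethnic groups or environment contexts as follows", and lists four groups of 32. Participants (Methods) describes 32 per group as an initial estimate from an effect size of 0.8 at alpha .05. The Discussion says the researchers will be guided by the recommended sample size, without giving a number.

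**The concern.** The text and the table it cites differ by a factor of ten on the assumption that drives the sample size. A reader who takes the text at its word would conclude that the study was sized for a very large effect and could not reproduce 88. The adjective makes this worse. If 0.120 is medium, a moderately large value should exceed it; 0.625 does, but 0.0625 does not. The wording therefore points to the wrong figure.

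The second problem is the target. The article gives 128 as a present intention and 88 as the computed need, and never connects the two. The Research Aims make determining the sample size a purpose of this article, so the final number belongs here. The choice also affects the hypotheses, which compare pairs of groups, whereas Table 2 sizes a single test across all four.

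**Working it through.** **Inputs.** k=4 groups, p=3 responses, alpha 0.05 and target power 0.80 (Table 2). f²=0.0625 (Table 2) or 0.625 (text). Pilot V=0.107 with N=30 in two groups (Results).

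**Formulas (Pillai V, noncentral F).** s=min(k−1, p); df1=p(k−1); df2=s(N−k−p+s); λ=N·s·f²; V=s·f²/(1+f²). Power is the probability that a noncentral F with these values exceeds the critical F.

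**1. Table 2 with f²=0.0625, N=88.** s=3 and df1=9.
- df2=3×(88−4−3+3)=252
- λ=88×3×0.0625=16.5
- V=0.1875/1.0625=0.1765
- Critical F=1.9171, power=0.8094

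Every output matches. With equal groups, 88 is the smallest total that reaches 0.80.

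**2. The same calculation with f²=0.625.** The smallest equal-group total is N=12.
- df2=3×(12−4−3+3)=24
- λ=12×3×0.625=22.5
- Critical F=2.300, power=0.818
- V=1.875/1.625=1.154

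At N=88, λ would be 165 and power about 1.00. The value in the text cannot have produced Table 2.

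**3. Pilot value.** With two groups s=1, so f²=0.107/(1−0.107)=0.120. With N=30, λ=3.6 and df 3 and 26, power is 0.284 against the stated 0.283. The ratio of planning to pilot value is 0.0625/0.120=0.52.

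**4. Targets.** 4×32=128 and 4×22=88. The difference is 40 children, or 40/128=31%.

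**5. Power at each target, by test.** The pairwise rows use k=2, p=3, s=1, df1=3 and df2=N−4.

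| Test | f² | 22 per group | 32 per group |
|---|---|---|---|
| Four-group global | 0.0625 | 0.81 | 0.95 |
| Two-group, three outcomes | 0.0625 | 0.23 (λ=2.75) | 0.34 (λ=4.00) |
| Two-group, three outcomes | 0.120 | 0.42 (λ=5.28) | 0.60 (λ=7.68) |

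Applying 0.0625 to a two-group test is an assumption, because the document gives no separate pairwise planning value. The value 0.120 is itself a two-group estimate, but from 30 children at resting baseline only.

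**The case against.** The effect-size conflict can be resolved from the document. The paragraph cites Table 2, and all of Table 2 follows from 0.0625, so 0.625 is very probably a misplaced decimal point that entered no calculation. This stands. A reader might infer that 88 is wrong, that the planning assumption is unknown, or that the design can detect only very large effects. The table supports none of these. The total of 12 shows only that the text value did not generate the result.

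The two targets are partly a sequence: 32 is called initial, and the sample size is then recomputed. Recruiting more than a computed minimum is also no contradiction in itself. This too stands, but it leaves the gap open. The Abstract still states 128 as the intention, and no passage says that 22 replaces 32 or that 22 is a floor beneath it.

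A reader might also infer that the older basis for 32 per group (d=0.80, alpha .05, and .80 printed as a *P* value) is wrong. The documents do not show this. The test and its sidedness are not stated, and the estimate rests on a cited study that is not at hand. At most, if .80 means power for a two-sided two-sample t-test, 26 per group would suffice (0.81) and 32 gives 0.88, so 32 would be more than enough.

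Finally, 0.95 at N=128 might be read as showing that the study is well powered for its hypotheses. It belongs to the four-group global test and says nothing about a pairwise comparison.

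**Conclusion.** The point holds as one misstatement and one omission. The text of Power and Sample Size Analysis misstates by a factor of ten the effect size behind its own result, and the label attached to it does not fit the value used. Table 2 is internally correct, and N=88 is right for its inputs. The final recruitment target is not stated: 128 and 88 both stand, 40 children apart.

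The factor of ten and the gap of 40 come directly from the document. The recomputed powers rest on the Pillai V approximation that reproduces Table 2, on equal groups and on complete data. The pairwise figures also rest on the effect sizes assumed in the working. Because this is an exploratory cross-sectional study and the table settles the effect size, the remedy is a correction and a clarification. Neither the unresolved target nor the test to which a quoted power belongs should be left for the reader to guess.

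**What to change.** 1. In Power and Sample Size Analysis, change f²=0.625 to f²=0.0625 and delete the words describing it as moderately large.
2. State one final target, in the same terms, in the Abstract, in Participants and in Power and Sample Size Analysis. If it is 128 (32 per group), say so and label 88 as the computed need for the four-group global test only. If it is 88, change the Abstract and Participants to match.
3. Name the test beside every power figure. For the global test at f²=0.0625: 0.81 at N=88 and 0.95 at N=128. For the pairwise three-outcome MANOVA with 22 and 32 per group: 0.23 and 0.34 at f²=0.0625, or 0.42 and 0.60 at the pilot value of 0.120.

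If 128 is kept, the cost is wording only and recruitment does not change. Choosing 88 means 40 fewer children and the lower pairwise power shown.

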## Discussion

Our initial data suggest that ample sample size is needed to demonstrate our concepts and prove our hypothesis, given our methods. Although our initial findings currently yield nonsignificant results, the lack of differences in the regulation of response between our sampled groups might be due to underpowered sample size; hence, the researchers shall be guided with the recommended ample sample size in the offing.

Although there is much that remains to be done, our work has future important findings in the field. The development of the ability to regulate responses to sensory stimuli does not occur in a vacuum, and some other variables (ie, cultural, anthropological, socioeconomic) may likely account for variations. Although we will collect several measures of socioeconomic status (ie, school attended, whether public or private; number of parents working; primary caregiver; highest educational attainment of caregiver; family income; and parent’s occupation) and proxy cultural measures (ie, parent-reported behavioral profiles of the child) and try our best to control for their confounding effects through sample stratification and statistical measures, their main effects are beyond the scope of this research. In this research, we mainly aimed to explore the influence of ethnicity and environment to explain differences in the regulation of response to sensory stimuli among typically developing school-aged children through indexing physiological autonomic measures from a biomedical and neurophysiological perspective.

Regulation of sensory responses from the environment is essential in daily activities. Some children may have difficulty in processing sensory information. However, the underlying mechanism contributed to the regulation of behavior toward sensory stimulation is not clearly understood yet. The answer that our research will eventually provide has several implications. First, our findings may further strengthen the role of individual differences on behavioral and physiological responses, adding to the body of literature that supports the theory of allostasis. Second, our future findings may influence the reconceptualization of the neurophysiological mechanisms behind the regulation of response to sensory stimuli. Third, if our hypotheses are correct, then our findings may influence the review and further development of behavioral outcome measures of regulation of response to sensory stimuli to constitute questionnaire constructs related to physiological symptoms, rather than on purely behavioral ones alone. Finally, this research may further inform clinical practice on the importance that a child’s external environment may play in the regulation of response to sensory stimuli, and consequently, consider these factors in intervention planning for children from clinical populations with diverse ethnic environments.

## Abbreviations

Ag/AgCl: silver-silver chloride
ANOVAs: analyses of variance
ANS: autonomic nervous system
BMI: body mass index
CDA: continuous decomposition analysis
CYRM: child and youth resilience measure
DV: dependent variable
EDA: electrodermal activity
HF: high frequency
HF (n.u.): high frequency (normalized unit)
HRV: heart rate variability
IV: independent variable
LF: low frequency
LF (n.u.): low frequency (normalized unit)
MANCOVA: multivariate analysis of covariance
MANOVA: multivariate analysis of variance
PNS: parasympathetic nervous system
SCL: skin conductance level
SCP: Sensory Challenge Protocol
SCR: skin conductance response
SNS: sympathetic nervous system
